### Statistical analysis

All data will be analysed by intention to treat. Comparisons between the primary outcome measure will be made at two separate time points: 6 months and 1 year to assess both short and long-term effects of the exercise intervention.

For outcomes measured on a continuous scale (MLwHF questionnaire, HADS, Euroqol, blood pressure, self-reported physical activity, distance walked on ISWT), differences between the two groups will be investigated using a least squares regression framework. Differences in time related clinical outcomes (hospital readmission rates, mortality and composite of these) will be analysed using the Kaplan-Meier survival method and the two groups compared by the Log-Rank test. Multivariate regression methods will be used to take into account the baseline measurements for each patient. When baseline information is available this provides a more precise estimate of the treatment effect than either raw outcomes or change scores[40]. Results will be expressed as means and 95% confidence intervals.

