**Methods/design:**

Randomised controlled trial comparing specialist heart failure nurse care plus a nurse-led predominantly home-based exercise intervention against specialist heart failure nurse care alone in a multiethnic city population, served by two NHS Trusts and one primary care setting, in the United Kingdom.

169 English speaking patients with stable heart failure, defined as systolic impairment (ejection fraction ≤ 40%). with one or more hospital admissions with clinical heart failure or New York Heart Association (NYHA) II/III within previous 24-months were recruited.

Main outcome measures at 1 year: Minnesota Living with Heart Failure Questionnaire, incremental shuttle walk test, death or admission with heart failure or myocardial infarction, health care utilisation and costs. Interviews with purposive samples of patients to gain qualitative information about acceptability and adherence to exercise, views about their treatment, self-management of their heart failure and reasons why some patients declined to participate.

The records of 1639 patients managed by specialist heart failure services were screened, of which 997 (61%) were ineligible, due to ejection fraction>40%, current NYHA IV, no admission or NYHA II or more within the previous 2 years, or serious co-morbidities preventing physical activity. 642 patients were contacted: 289 (45%) declined to participate, 183 (39%) had an exclusion criterion and 169 (26%) agreed to randomisation.

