### Outcome measures

Follow-up by postal questionnaire and clinical assessment occurs at 6 months and by postal questionnaire at 1 year.

The primary outcome measure is the Minnesota Living with Heart Failure Questionnaire (MLwHF) Questionnaire[37]. Secondary outcome measures at 6 months are (i) composite of death or admission with heart failure or myocardial infarction, (ii) admission with heart failure, (iii) mortality (all-cause and vascular), (iv) EuroQol[38], (v) HADS[39], (vi) blood pressure, (vii) self-reported physical activity, and (viii) distance walked on the ISWT[36]. At 12 months the ISWT and blood pressure measurements are omitted.

Process measures to determine the comparability of intervention received from the specialist heart failure service included self-reported smoking cessation, salt reduction and alcohol intake. Uptake and adherence to the exercise intervention are assessed by (i) attendance at the hospital training sessions, and (ii) patient completed exercise diaries at 4, 10 and 20 weeks in the intervention group.

The study could not be double blind because of the nature of the intervention. To reduce the potential for bias in measuring outcomes in the questionnaires we used validated measurement tools and aimed for clinical follow-up to be undertaken by an individual who had not provided the rehabilitation support and was blinded to treatment allocation. Determination of secondary end-points (hospitalisation for heart failure and vascular mortality) was by an independent committee blinded to treatment allocation.

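### Kaplan-Meier curves for heart-failure admission and vascular death would modestly overstate incidence, the composite is worded differently in two sections, and MI admission is not named in the blinded committee's remit

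*Protocol article*

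**What the plan says.** Under Outcome measures, the first secondary outcome is the "composite of death or admission with heart failure or myocardial infarction". The list continues with "ii) admission with heart failure, (iii) mortality (all-cause and vascular". The abstract (Methods/design) names the same three-part composite among the main outcomes at 1 year: "death or admission with heart failure or myocardial infarction, health care utilisation and costs".

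Under Statistical analysis, the event outcomes are described differently: "Differences in time related clinical outcomes (hospital readmission rates, mortality and composite of these) will be analysed using the Kaplan-Meier survival method", with "the two groups compared by the Log-Rank test". No cause of readmission is given, MI is not named, and no method for competing events is mentioned. The paragraph then plans multivariate regression to account for baseline measurements, and ends: "Results will be expressed as means and 95% confidence intervals".

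On ascertainment, Outcome measures states: "The study could not be double blind because of the nature of the intervention". It then says: "Determination of secondary end-points (hospitalisation for heart failure and vascular mortality) was by an independent committee blinded to treatment allocation".

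**The concern.** Three things in these sections do not fit together.

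- **Competing deaths.** Heart-failure admission can no longer occur after death, and vascular death can no longer occur after non-vascular death. Kaplan-Meier treats such patients as censored, as if they could still have the event later. One minus the curve then exceeds the proportion who actually have it. If admission hazards are equal, the excess is larger in the arm with more deaths.
- **Which composite.** Taken literally, the analysis sentence combines readmission for any cause with death. That is a different endpoint from death, heart-failure admission or MI admission. The Discussion expects much co-morbidity, so admissions for other causes could be common and would dilute the declared composite. Readmission is also an awkward term, because the abstract allows entry on NYHA class II/III as an alternative to a previous admission.
- **Who judges MI.** Classifying an admission as MI takes judgement. In a trial that is not double blind, a component with no stated blinded determination leaves room for ascertainment bias.

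These outcomes matter to the trial's purpose. The rationale section says follow-up had to be long enough to measure admissions and mortality. The Economic analysis takes life years from the mortality analysis and costs admissions linked to heart failure.

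**Working it through.** **No event figure to reproduce.** The article gives no event rate, event count, hazard ratio or power for the clinical events, so the rates below are assumptions. The only anchor is the Sample Size section's 20% allowance for mortality and loss to follow-up combined. Because the split is not given, 20% is used as a ceiling for 1-year death risk.

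**Size of the Kaplan-Meier excess for heart-failure admission.** Assume constant hazards, with a 1-year death risk d of 5% to 20% and a 1-year admission risk a of 10% to 30% when deaths are censored.

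- Hazards: ld = −ln(1 − d) and la = −ln(1 − a).
- One minus Kaplan-Meier at time t: 1 − exp(−la·t).
- Cumulative incidence: [la/(la + ld)] × [1 − exp(−(la + ld)·t)].

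Worked middle case (d = 10%, a = 20%, t = 1): ld = 0.1054 and la = 0.2231, which sum to 0.3285. Then exp(−0.3285) = 0.9 × 0.8 = 0.72. Cumulative incidence = (0.2231/0.3285) × 0.28 = 19.0%, against 20.0% by Kaplan-Meier.

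| Death risk d | Admission risk a (1 − KM, 1 year) | Cumulative incidence | Excess (points) | Relative excess |
|---|---|---|---|---|
| 5% | 10% | 9.75% | 0.2 | 2.5% |
| 10% | 20% | 19.0% | 1.0 | 5.2% |
| 20% | 20% | 18.0% | 2.0 | 11.1% |
| 20% | 30% | 27.1% | 2.9 | 10.8% |

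Over the whole grid the excess is 0.2 to 2.9 points at 1 year, and 0.1 to 0.9 points at 6 months.

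**Vascular death.** As an illustration, let 20% die in the year, half from vascular causes at equal constant hazards. Cumulative incidence of vascular death is 0.5 × 20% = 10.0%. Kaplan-Meier with non-vascular deaths censored gives 1 − √0.8 = 10.6%, an excess of about 0.6 points.

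**Difference between arms.** Let the admission hazard be the same in both arms and the death hazard ratio be 0.65 (the pooled estimate quoted in the Background). For control death risks of 10% and 20% and the admission risks above, true cumulative incidence differs between arms by 0.2 to 1.0 points, while the Kaplan-Meier curves coincide. For scale, the standard error of a difference in proportions near 18% with 84 per arm is √(2 × 0.18 × 0.82/84) = 5.9 points.

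**Composite and adjudication, side by side.**

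| | Outcome measures | Abstract | Statistical analysis | Blinded committee |
|---|---|---|---|---|
| Death | any cause, in the composite | yes | mortality | vascular mortality named |
| Heart-failure admission | yes | yes | readmission, cause not given | named |
| MI admission | yes | yes | not named | not named |

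Two sections agree on the composite and the analysis section does not. MI admission is the one admission component missing from both right-hand columns.

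**The case against.** The strongest reply is that this is a condensed article and that censoring rules and competing-event handling usually sit in a full protocol or analysis plan, which is not shown. It is true that nowhere does the article say deaths are censored. That follows from the method it does name: Kaplan-Meier applied to a non-fatal or cause-specific event has no other standard treatment of those deaths.

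A reader might infer that the event analysis as a whole is invalid. It is not. The log-rank test with deaths censored is a valid comparison of cause-specific hazards. All-cause death and a composite that includes death have no competing death to mishandle. Only a curve read as incidence is biased, and the distortion between arms is small beside the sampling error.

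A reader might also infer that no effect size will be reported for clinical events. The text does not support that, since the same paragraph plans regression and 95% intervals without limiting them to continuous outcomes. What stands is that no hazard model is named and that a mean does not express a time-to-event result.

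The analysis section's composite may be shorthand for outcomes already defined; it shortens the mortality outcomes in the same way. That is plausible, and nothing shows an intention to count different events. The wording still lets two analysts count differently.

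Finally, it is tempting to say that MI admissions went unadjudicated or were judged unblinded. The article says neither. It is silent, and the two bracketed end-points may be only examples. Nor does the article rank the composite above the other secondary outcomes; it only lists it first.

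**Conclusion.** The point holds in limited form and is worth acting on. Kaplan-Meier for heart-failure admission and vascular death would overstate incidence by about 0.2 to 2.9 percentage points at 1 year. This assumes constant hazards, a 1-year death risk of 5% to 20% and a censored-deaths admission risk of 10% to 30%; none of these rates comes from the article except the 20% ceiling. The composite in the analysis section does not match the one defined elsewhere, and the stated reporting scale does not suit event outcomes. MI admission lies outside the stated scope of blinded adjudication. The primary quality-of-life comparison is untouched.

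**What to change.** - For heart-failure admission, present cumulative incidence curves with death as a competing event. For vascular mortality, do the same with non-vascular death as the competing event. Keep the log-rank test, described as a cause-specific comparison, and add cause-specific hazard ratios with 95% intervals.
- Keep Kaplan-Meier for all-cause death and for the composite.
- In the Statistical analysis section, define the composite exactly as under Outcome measures, and restrict the reference to means to the continuous outcomes.
- State that MI admissions go to the existing blinded committee.

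The cost is revised wording, slightly more analysis and a few extra case summaries for a committee that already exists. No change to design or sample size is needed.

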## Methods/Design

BRUM-CHF is a randomised controlled trial of exercise rehabilitation in heart failure comparing specialist heart failure nurse care alone with specialist heart failure nurse care plus a structured exercise intervention.

Prior to commencement of the study, ethical approval was obtained from Sandwell and West Birmingham Local Research Ethics Committee (Reference number: 03/10/708).

Randomisation was performed centrally by computer at the Birmingham Cancer Clinical Trials Unit, University of Birmingham. When a patient was identified as eligible for the study, and had given written, informed consent to take part, the research nurse telephoned the trials unit. The Trials Unit randomly allocated patients, using the method of minimisation, stratified by (i) NYHA group, (ii) presence or absence of atrial fibrillation and (iii) hospital site.

In one arm patients continued with "usual" specialist heart failure nurse care. In the other arm patients continued with "usual" specialist heart failure nurse care combined with the exercise programme. The trial design is summarised in Figure 1. Patients who refused randomisation continued with their normal specialist nurse care.

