### Population

The two NHS hospital Trusts and one Primary Care Trust from which patients were recruited are in the West Midlands, UK, covering a combined multiethnic population of approximately one million with a high incidence of heart disease. Recruited patients had left ventricular systolic dysfunction with an ejection fraction of 40% or less measured quantitatively, or classed qualitatively as 'moderate to severe impairment' on an echocardiogram, and were identified from three specialist heart failure nurse services. Recruitment took place over 19 months. Inclusion and exclusion criteria are summarised in Table 1.

Details of all patients referred to the specialist heart failure services were collected and suitability for study participation identified. Potentially eligible patients were contacted, invited to participate and assessed prior to randomisation by an incremental shuttle walk test (ISWT) to determine their suitability for exercise and to exclude patients with symptomatic ischaemia, cardiac arrhythmias or marked hypotension on exercise[34,35].

Baseline data collected prior to randomisation included the NYHA class, left ventricular systolic ejection fraction, demographic details (age, sex, ethnicity), disease history (admissions for heart failure) and past medical history, current medication, and outcomes (see below).

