### Sample Size

The overall power of the trial was determined on the basis of the primary outcome – health related quality of life.

To detect a 10 point difference between the 'usual care' and supervised exercise group on the MLwHFQ (13 points at 1 year in Belardinelli)[22] at the 5% significance level with 80% power, 140 evaluable subjects at 1 year were needed. Allowing for 20% mortality and loss to follow-up a total of 168 recruits (84 per group) were needed.

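### The minimisation factors (NYHA group, atrial fibrillation, hospital site) are not named in the stated analysis, which may make intervals too wide and tests conservative

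*Protocol article*

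**What the plan says.** In the protocol article, Methods/Design says that the trials unit allocated patients "using the method of minimisation, stratified by (i) NYHA group, (ii) presence or absence of atrial fibrillation and (iii) hospital site".

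The Statistical analysis section covers two kinds of outcome. For continuous outcomes, "differences between the two groups will be investigated using a least squares regression framework". For hospital readmission, mortality and their composite, the plan is the "Kaplan-Meier survival method and the two groups compared by the Log-Rank test". It then adds: "Multivariate regression methods will be used to take into account the baseline measurements for each patient". The reason given is that, where baseline information exists, "this provides a more precise estimate of the treatment effect than either raw outcomes or change scores". None of the three minimisation factors appears in that section, and no strata are given for the log-rank test.

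The Population section bears on what counts as baseline: "Baseline data collected prior to randomisation included the NYHA class, left ventricular systolic ejection fraction", followed by demographic details, disease and medical history, medication and the outcomes themselves.

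**The concern.** Minimisation makes the arms alike on the chosen factors. If those factors are related to outcome, the treatment difference varies less from one hypothetical trial to the next than it would under simple randomisation. A model without the factors cannot see this. It leaves their contribution in the residual variance and reports a standard error suited to a less balanced design.

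The consequence is lost precision, not a misleading estimate: intervals wider than they need be, and tests that reject too seldom under the null. Results are to be presented as means with 95% confidence intervals, so interval width is part of what the trial reports.

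**Working it through.** **Inputs.** From the documents: the minimisation factors (Methods/Design), the regression and log-rank test (Statistical analysis) and the 5% level (Sample Size; taken as two-sided, since sidedness is not stated). Not in the documents: R², the share of outcome variance left after the baseline score that the three factors explain. I take 0%, 5%, 10% and 20%. The plan gives no figure of its own on this point to reproduce.

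**Step 1, formula.** Let σ² be the residual variance after adjusting for the baseline outcome, with N patients split equally.

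- Squared standard error reported without the factors: 4σ²/N.
- Actual variance of the estimate when the factors are balanced: 4σ²(1 − R²)/N.
- Reported over actual standard error: 1/√(1 − R²).
- Actual level of a nominal 5% test: 2[1 − Φ(1.96/√(1 − R²))].

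| Assumed R² | Reported/actual SE | Interval too wide by | Actual level |
|---|---|---|---|
| 0% | 1 | 0% | 5.0% |
| 5% | 1/√0.95 = 1.026 | 2.6% | 2[1 − Φ(2.011)] = 4.4% |
| 10% | 1/√0.90 = 1.054 | 5.4% | 2[1 − Φ(2.066)] = 3.9% |
| 20% | 1/√0.80 = 1.118 | 11.8% | 2[1 − Φ(2.191)] = 2.8% |

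Neither σ nor N enters the ratio or the level.

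**Step 2, simulation of the regression.** The formula assumes exact balance, so it was checked by simulating deterministic minimisation on three factors. Assumptions: 140 evaluable patients, three sites, assumed factor prevalences, baseline-outcome correlation 0.5, SD 21.1 and about 3,000 runs per scenario. The SD only sets the scale. It is back-solved from "at the 5% significance level with 80% power, 140 evaluable subjects at 1 year were needed" for a 10-point difference: 10 × √(70/2)/(1.96 + 0.84) ≈ 21.1.

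| Assumed R² | Model SE, baseline only | True SE of that estimate | Model SE, factors added | Type I error, baseline only | Type I error, factors added |
|---|---|---|---|---|---|
| 0% | 3.09 | 3.16 | 3.09 | 0.054 | 0.056 |
| 5% | 3.09 | 2.99 | 3.02 | 0.041 | 0.044 |
| 10% | 3.10 | 2.94 | 2.94 | 0.039 | 0.048 |
| 20% | 3.09 | 2.79 | 2.77 | 0.030 | 0.051 |

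Simulation error on a rate near 0.05 is √(0.05 × 0.95/3000) ≈ 0.004. At 10%, 3.10/2.94 = 1.054; at 20%, 3.09/2.79 = 1.108. Both are in line with step 1. At 0%, adding the factors leaves the model SE unchanged.

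**Step 3, simulation of the log-rank test.** 169 patients, 2,500 runs, about 44 to 49 events under the null.

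| Assumed prognostic effect | Type I error, plain | Type I error, stratified by NYHA and atrial fibrillation |
|---|---|---|
| None | 0.053 | 0.050 |
| Moderate | 0.043 | 0.050 |
| Strong | 0.035 | 0.052 |

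Simulation error is √(0.05 × 0.95/2500) ≈ 0.0044, so the moderate result is suggestive and only the strong one is clearly below 5%.

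**Step 4, how finely to stratify.** Crossing all three factors gives 2 × 2 × 3 = 12 cells. With a strong prognostic effect, an assumed halving of the hazard and about 38 events, the 12-cell test rejected in 0.525 of runs, against 0.553 with the four NYHA-by-atrial-fibrillation strata.

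**The case against.** **The article leaves the factors unnamed; it does not exclude them.** It gives no covariate list. Its wording on baseline measurements is plural, NYHA class is listed among the baseline data, atrial fibrillation could fall under medical history, and the adjustment sentence directly follows the log-rank sentence, so it may extend to events. This stands in part: the article cannot be said to rule the factors out. But the reason given contrasts the adjustment with raw outcomes and change scores, which fits the baseline value of the outcome. The wide reading would bring in every item of baseline data, which does not define a model. Site is not in the Population section's list, and the log-rank test is stated without strata.

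**Covariate lists and strata are commonly left to the full protocol or analysis plan.** This is true, and if those documents name the factors the point is met. The article does, however, choose an adjustment, justify it and name the event test. Those choices do not use the balance that the design creates.

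**The size is assumed.** This stands. What counts is prediction beyond the baseline score, which may already carry much of what NYHA class says, and patients in current NYHA IV were excluded. The effect on the primary outcome could be only a few percent of the standard error. Loss to follow-up, or a random element in the minimisation, would also loosen the balance, so for a given R² the step 1 figures are upper values.

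**A reader might infer that the trial is short of power and that adjustment would restore a known amount.** The documents do not support that. No SD is stated. The 21.1 is back-solved for an unadjusted comparison, whereas the planned analysis adjusts for baseline. With 67 per arm (168 × 0.8 = 134.4 evaluable) and a 10-point difference, an SD of 21.1 gives about 78% power. An assumed correlation of 0.5 reduces the SD to 21.1 × √0.75 ≈ 18.3 and gives about 89%. Whether there is any shortfall therefore depends on figures the article does not give.

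**Conclusion.** The point holds as a mismatch between the stated allocation and the stated analysis, with a conditional cost. If the factors explain an assumed 5%, 10% or 20% of the variance left after the baseline score, intervals are about 2.6%, 5.4% or 11.8% too wide and the nominal 5% test runs at about 4.4%, 3.9% or 2.8%. The plain log-rank test moves in the same direction. If the factors have no prognostic value, there is no loss.

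It would be wrong to conclude that the treatment estimate is biased or that false positives are inflated: the error is on the conservative side. It would equally be wrong to say without condition that the intervals are too wide, because the strength of the factors is not documented. This is an inexpensive improvement to make before analysis; it does not invalidate the planned comparison.

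**What to change.** State in the Statistical analysis section that every continuous-outcome regression includes NYHA group, atrial fibrillation and hospital site as covariates, alongside the baseline value of that outcome.

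For time-to-event outcomes, replace "the two groups compared by the Log-Rank test" with either a Cox model adjusted for the three factors, its hazard ratio labelled as conditional on them, or a log-rank test stratified by a small number of them. Avoid crossing all three factors into strata, which loses some power when events are few. Kaplan-Meier curves can stay as description.

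If the present wording was already meant to include these factors, one sentence saying so is enough. The cost is wording only: the factors were recorded at randomisation, so no further data are needed. Make the change before outcomes are compared by arm, so that the covariates cannot be chosen in the light of results.
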